## 8.5 Reporting Procedure

Then flow chart describes the SAE reporting procedure:

[figure not shown]

Unexpected SAEs must be reported by the investigator to the sponsor, [name], using the Oslo University Hospital reporting system Achilles, within 24 hours after the site has gained knowledge of the unexpected SAE. Sponsor should also be notified via telephone or SMS at [name] when a report is sent.

Every SAE must be documented by the investigator on the SAE pages as part of the CRF. The Serious Adverse Event Report Form must be completed, signed and sent to [name]. The initial report shall promptly be followed by detailed, written reports if necessary. The initial and follow-up reports shall identify the trial subjects by unique code numbers assigned to the latter.

The sponsor keeps detailed records of all SAEs reported by the investigators and performs an evaluation with respect to seriousness, causality and expectedness.

### 8.5.1 SUSARs

SUSARs will be reported to the Competent Authority and Ethics Committee according to national regulation. The following timelines should be followed:

The sponsor will ensure that all relevant information about suspected serious unexpected adverse reactions that are fatal or life-threatening is recorded and reported as soon as possible to the Competent Authority and Ethics Committee in any case no later than seven (7) days after knowledge by the sponsor of such a case, and that relevant follow-up information is subsequently communicated within an additional eight (8) days. All other suspected serious unexpected adverse reactions will be reported to the Competent Authority concerned and to the Ethics Committee concerned as soon as possible but within a maximum of fifteen (15) days of first knowledge by the sponsor.

SUSARs will be reported using the CIOMS form since Oslo University Hospital is not connected to EudraVigilance.

### **8.5.2 Annual Safety Report**

Once a year throughout the clinical trial, the sponsor will provide the Competent Authority with an annual safety report. The format will comply with national requirements.

### **8.5.3 Clinical Study Report**

The adverse events and serious adverse events occurring during the study will be discussed in the safety evaluation part of the Clinical Study Report. The report will be sent to the Norwegian Medicines Agency within one year of the completion or discontinuation of the trial.

## **8.6 Procedures in Case of Emergency and unblinding**

The principal investigator is responsible for assuring that there are procedures and expertise available to cope with emergencies during the study prior to including patients in this trial.

For medical emergencies during treatment in this trial the standard operating procedures for the participating department will be followed. For pre-hospital sites this includes telephone or radio contact with colleague via AMK, with the potential for additional recourses to be dispatched to the scene.

For participating departments in-hospital this includes calling on help from senior aides or other recourses via normal hospital procedures.

If the study doctor considers iNO treatment mandatory or contra indicated for patient benefit, he or she may perform emergency unblinding. This is done by a closed loop communication procedure in which the study doctor clearly states an intention of unblinding as well as the reason for unblinding. The assistant repeats back to the study doctor for confirmation, before revealing the allocation. The reason for emergency unblinding is recorded in the CRF as soon as practicably possible. The emergency blinding procedure will be described in the written instructions for the study doctor and the assistant.

## **8.7 Data Monitoring Committee (DMC)**

A DMC will be recruited. Their work will be described in a charter based on the NORCRIN Standard Operating Procedure. This describes the roles and responsibilities of the DMC, including the timing of meetings, methods of providing information to and from the DMC, frequency and format of meetings, statistical issues and relationships with other Sponsor. The charter and the DMC should be in place before the first patient is included.

The DMC will meet after the interim analysis, and in the event of SUSAR reporting.

## 9 DATA MANAGEMENT AND MONITORING

Data management will be performed by the data management unit at the Clinical Trials Unit, Oslo University Hospital. The Data management procedures will be performed in accordance with the department's SOPs and ICH guidelines. The data management process will be described in the study specific Data Handling Plan and the study specific Data Handling Report after database closure.

Data entered into the eCRF will be validated as defined in the Data Validation Plan. Validation includes, but is not limited to, validity checks (e.g. range checks), consistency checks and customized checks (logical checks between variables to ensure that study data are accurately reported) for eCRF data and external data (e.g. laboratory data). A majority of edit checks will be triggered during data entry and will therefore facilitate efficient 'point of entry' data cleaning.

Data management personnel will perform both manual eCRF review and review of additional electronic edit checks to ensure that the data are complete, consistent and reasonable. The electronic edit checks will run continually throughout the course of the study and the issues will be reviewed manually online to determine what action needs to be taken.

Manual queries may be added to the system by clinical data management or study monitor. Clinical data managers and study monitors are able to remotely and proactively monitor the patient eCRFs to improve data quality.

All updates to queried data will be made by authorized study center personnel only and all modifications to the database will be recorded in an audit trail. Once all the queries have been resolved, eCRFs will be signed by electronic signature. Any changes to signed eCRFs will be approved and resigned by the Investigator.

Adverse events will be coded from the verbatim description (Investigator term) using the Medical Dictionary for Regulatory Activities (MedDRA).

Once the full set of eCRFs have been completed and locked, the Sponsor will authorize database lock and all electronic data will be sent to the designated statistician for analysis. Subsequent changes to the database will then be made only by written agreement.

The data will be stored in a dedicated and secured area at Oslo University Hospital. Data will be stored in a de-identified manner, where each study participant is recognizable by his/her unique trial subject number. The data will be stored until 15 years following the last patient's final study visit.

## 9.1 Case Report Forms (CRFs)

Two paper CRFs will be produced.

1: For treatment visit, this will capture data on primary end point, length of intervention and details regarding IMP administration, protocol adherence and main safety data not captured in other source data. This will be filled in by treating doctor/ investigator administering IMP

2: day 28 visit

This will be filled out by investigator if patient admitted to OUH, or by treating doctor in cooperation with investigator if patient admitted to hospital outside OUH. This will capture secondary and explorative endpoint as described earlier, including safety data.

## 9.2 Source Data

Source data in this trial includes study specific paper case report form. In addition, all patient records may be sources of specific information. For patients in this trial this includes:

- Study specific paper CRF inclusion visit and day 28 visit
- Prehospital paper records, computer notes in LABAS, records in AMIS and sound or in medical dispatch system.
- Records from medical monitors such as LP15 and CorPulse
- In-hospital results in DIPS or other EPJ
- Interview with study workers or treating physician in hospital

|   | Objectives                                                                                                                                                                         |       | Endpoints                                                     | Source data with hierarchy if inconsistent data between sources |
|---|------------------------------------------------------------------------------------------------------------------------------------------------------------------------------------|-------|---------------------------------------------------------------|-----------------------------------------------------------------|
|   | Primary                                                                                                                                                                            |       | Primary                                                       |                                                                 |
| 1 | Evaluate the clinical efficacy of iNO to increase oxygen saturation prior to, during and after emergency RSI in patients with suspected or confirmed COVID-19 respiratory failure. | 1.1.1 | $\Delta \text{SpO}_2$                                         | CRF > Patient monitor > Patient paper chart > Patient EPJ       |
|   |                                                                                                                                                                                    |       | Secondary                                                     |                                                                 |
|   |                                                                                                                                                                                    | 1.2.1 | $\Delta \text{SpO}_2 (t_0-t_2)$                               | CRF > Patient monitor > Patient paper chart > Patient EPJ       |
|   |                                                                                                                                                                                    | 1.2.2 | $\text{SpO}_2$ during RSI ( $t_{\text{RSI}}$ )                | CRF > Patient monitor > Patient paper chart > Patient EPJ       |
|   |                                                                                                                                                                                    | 1.2.3 | $\text{SpO}_2$ from $t_1 - t_n$                               | Patient monitor > Patient chart > Patient EPJ                   |
|   |                                                                                                                                                                                    | 1.2.4 | Number of patients with $\text{SpO}_2 < 50$ from $t_1$ to EOI | CRF > Patient monitor > Patient paper chart Follow up visit CRF |

|    |                                                                                                                             |                             |       |                                                                             |                                                           |
|----|-----------------------------------------------------------------------------------------------------------------------------|-----------------------------|-------|-----------------------------------------------------------------------------|-----------------------------------------------------------|
|    |                                                                                                                             |                             | 1.2.5 | Respiratory rate from t 0 to t RSI or EOI             | Patient monitor > Patient paper chart > Patient EPJ       |
|    |                                                                                                                             |                             | 1.2.6 | PaO 2 at t 0 to EOI                                   | Follow up visit CRF > Patient EPJ                         |
|    |                                                                                                                             |                             | 1.2.7 | Cardiac arrest during intervention                                          | CRF                                                       |
|    |                                                                                                                             |                             | 1.2.8 | GOS-E score on day 28                                                       | Follow up visit CRF > Patient EPJ                         |
|    |                                                                                                                             |                             | 1.2.9 | Mortality                                                                   | Follow up visit CRF > Patient EPJ                         |
|    | Secondary                                                                                                                   |                             |       | Secondary                                                                   |                                                           |
| 2  | Evaluate the safety of the intervention as compared to the control as assessed by:                                          | 2.1
Circulatory function | 2.1.1 | Heart rate at t 0 -t n                                | Patient monitor > Patient chart > Patient EPJ             |
|    |                                                                                                                             |                             | 2.1.2 | Blood pressure at t 0 to t n                          | Patient monitor > Patient chart > Patient EPJ             |
|    |                                                                                                                             | 2.2
Kidney function      | 2.2.1 | Increase in Serum urea concentration                                        | Follow up visit CRF > Patient EPJ                         |
|    |                                                                                                                             |                             | 2.2.2 | KDIGO AKI Stage up to day 28                                                | Follow up visit CRF > Patient EPJ                         |
|    |                                                                                                                             | 2.3
Hemoglobin function  | 2.3.1 | Arterial MetHgb concentration                                               | Follow up visit CRF > Patient EPJ                         |
|    |                                                                                                                             | 2.4
Platelet count       | 2.4.1 | Platelet count                                                              | Follow up visit CRF > Patient EPJ                         |
|    |                                                                                                                             |                             | 2.5.1 | Need for iNO after EOI                                                      | Follow up visit CRF > Patient EPJ                         |
|    |                                                                                                                             |                             | 2.5.2 | ICD-10 diagnosis on discharge                                               | Follow up visit CRF > Patient EPJ                         |
|    | Exploratory                                                                                                                 |                             |       | Exploratory                                                                 |                                                           |
| 3. | Evaluate the clinical efficacy of iNO compared to standard treatment on respiratory severity and length of specialized care |                             | 3.1.1 | O 2 -ratio for patients on mechanical ventilation first 24 hours | Follow up visit CRF > Patient EPJ                         |
|    |                                                                                                                             |                             | 3.1.2 | PaCO 2 at t 0 to EOI                                  | Follow up visit CRF > Patient EPJ                         |
|    |                                                                                                                             |                             | 3.1.3 | EtCO 2 at t 0 to EOI                                  | CRF > Patient monitor > Patient paper chart > Patient EPJ |
|    |                                                                                                                             |                             | 3.1.4 | Ventilator free days up to day 28                                           | Follow up visit CRF > Patient EPJ                         |
|    |                                                                                                                             |                             | 3.1.5 | Length of stay in ICU                                                       | Follow up visit CRF > Patient EPJ                         |

|   |                                                          |       |                  |                                   |
|---|----------------------------------------------------------|-------|------------------|-----------------------------------|
| 4 | Evaluate the effect of INO on cardiac stress             | 4.1.1 | Serum troponin T | Follow up visit CRF > Patient EPJ |
|   |                                                          | 4.1.2 | ProBNP           | Follow up visit CRF > Patient EPJ |
|   | Patient Demographic variables                            |       |                  | Patient EPJ                       |
|   | Temporal and technical data regarding emergency dispatch |       |                  | AMIS > Patient paper chart        |
|   |                                                          |       |                  |                                   |
|   |                                                          |       |                  |                                   |

### 9.3 Study Monitoring

The investigator will be visited on a regular basis by the Clinical Study Monitor, who will check the following:

- Informed consent process
- Reporting of adverse events and all other safety data
- Adherence to protocol
- Maintenance of required regulatory documents
- Study Supply accountability
- Data completion on the CRFs including source data verification (SDV).

The monitor will review the relevant CRFs for accuracy and completeness and will ask the site staff to adjust any discrepancies as required.

Sponsor's representatives (e.g. monitors, auditors) and/or competent authorities will be allowed access to source data for source data verification in which case a review of those parts of the hospital records relevant to the study may be required.

### 9.4 Confidentiality

The investigator shall arrange for the secure retention of the patient identification and the code list following the guidelines set out by Oslo University Hospital and its Data Protection Officer. Patient files shall be kept for the maximum period of time permitted by each hospital. The study documentation (CRFs, Site File etc.) shall be retained and stored during the study and for 25 years after study closure. All information concerning the study will be stored in a safe place inaccessible to unauthorized personnel.

## 10 STATISTICAL METHODS AND DATA ANALYSIS

### 10.1 Determination of Sample Size

One previous study in a different setting has shown that 71% of patients respond to the treatment with an absolute increase in SpO2 of >5 percentage points(21). We assume a standard deviation of 10 percentage points, and a within subject correlation of 0.8 based on clinical experience. This implies a standard deviation of the change in SpO2 (before minus after intervention) of 6.32%. A difference in improvement in SpO2 of 5 percentage points between the intervention groups is considered clinically significant. To identify a difference of improvement of SpO2 of 5 percentage points, with a power of 80%, we need to include 54 patients (27 in each arm) in this trial, using a significance level of 5%. Because of the uncertainty related in the magnitude of the variance in the SpO2 change, a simple blind re-estimation of the sample size based on the variance from a subsample of the 20 first patients will be done. The sample size will be adjusted if necessary, but the total sample will not be reduced (to less than 54). By using a blinded one-sample variance estimator for sample size recalculation, the effect of sample size adjusting on the type I error rate is negligible and no additional measures are needed to control the significance level(22).

### 10.2 Randomization and Blinding

Eligible patients will be allocated in a 1:1 ratio between the two study arms, using a computer-based randomization procedure. The randomization will be blocked using varying block sizes. The randomization will be stratified between the study sites. Initially two study sites (Lørenskog and Ullevål) include patients for the study. If further sites are added during the trial, these will be treated as separate strata in the randomization.

The randomization list will be sent to the OUH Hospital Pharmacy division for clinical trial who will pack envelopes with labels indication allocation groups. The envelopes will not be able to see or light through, or open without breaking the seal. Sealed envelopes will be collected by the study team for placement on the bags contains IMP. An accountability form for all envelopes produces will be in place. Unopened envelopes will be returned to the Pharmacy.

The sealed envelope produced by the pharmacy will be placed in the iNO study kit. When a patient is found eligible, the envelope is opened by the study doctor's assistant. He or she will either open or mimic opening the INOmax cylinder according to allocation. The INOmax cylinder is contained in a bag, and the cylinder valve with the pressure gauge will not be visible to the study doctor.

The procedure of blinding and emergency unblinding will be described in a written instruction for both the study doctors and the assistants. Emphasis will be put on instructing the assistant not to take part in any study-relevant clinical decision-making or discussion about the clinical condition of the patient, including the option of emergency unblinding after randomization.

After arrival in hospital, after the patient is intubated or a decision is made not to perform intubation, the assistant will hand over the envelope containing the randomization as a part of the written treatment documentation. This is in the interest of further hospital patient care, and to evaluate additional need for iNO other than IMP. The allocation will thus be revealed to the personnel taking over responsibility for the patient,

but not to the study doctor. The study doctors are specifically instructed not to try to obtain information on allocation.

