### 3 OVERALL STUDY DESIGN

The study is a phase II drug trial of inhaled nitric oxide as an adjunct to standard of care with medical oxygen as part of airway management in patients with known or suspected covid-19 and who are in acute respiratory failure.

The trial is parallel two-arm, randomized, controlled blinded trial.

The primary outcome measure is the change in SpO2, and the null hypothesis is that there is no difference in the change in SpO2 following initiation of INO.

The trial is initiated as a single center study but is open for inclusion from other centers that have INO delivered by INOBlender as a treatment option.

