#### **Follow-up:**

After End of Intervention, participants will be followed up at day 28. This follow up visit will be a chart- review with or without interview with treating physician at main hospital admission from end of intervention till day 28. For patients still admitted at day 28 and discharged prior to end of trial their discharge note will be assessed.

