## 10.5 Statistical Analysis

Demographics and other baseline characteristics, such as age, gender etc., will be described for all randomized patients (the ITT population). Continuous variables will be described in terms of number of observations (n), mean value and standard deviation. All variables of a categorical nature will be displayed with frequencies and percentages. The tabulation of the descriptive statistics will be split by treatment group.

The primary efficacy endpoint, the difference in the change in SpO2 from before to after the intervention, will be analyzed using a linear regression model where the intervention variable will be adjusted by the baseline SpO2 and the stratification variable used in the randomization (study site). Currently there are two sites in this trial. If additional sites are added during the trial, these will represent additional strata. If the residuals from the regression model is not normally distributed, suitable transformations will be applied to the data or non-parametric alternatives will be used.

For the primary endpoint, a subgroup analysis will be performed according to later confirmed Covid-19 status of the patients. Presence of COVID-19 disease is classified as per WHO definition of confirmed COVID-19 (see ch 1.1.1), and with the SARS-CoV-2 test routine used at the given point of time in the respective institution. Data will be extracted from the EPJ on the 28-day visit.

Analyses of secondary endpoints will be performed in a similar manner as for the primary endpoint and/or using repeated measures mixed models for continuous variables, and logistic regression models for binary endpoints. Subgroup analyses will be performed according to later confirmed Covid-19 diagnosis for the secondary endpoints related to SpO2 (endpoints 1.2.1-1.2.4).

The primary and secondary analyses will be performed in the FAS, and robustness analyses will be performed in the PP population. A separate statistical analysis plan (SAP) will provide further details on the planned statistical analyses. The SAP will be finalized, signed and dated prior to database lock. The treatment allocation will be revealed after the database lock and used in the statistical analysis.

Deviation from the original statistical plan will be described and justified in the Clinical Study Report.

Amendments to plan can be done until day of database (DB) lock.

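### GOS-E and SAE judgements at day 28 draw on a chart and on doctors that carry the allocation, and nothing keeps the assessor from it

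*Protocol*

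**What the plan says.** Section 3 labels the study: "The trial is parallel two-arm, randomized, controlled blinded trial". It does not say who is blinded or until when. Section 10.2 sets out the mechanism. The assistant opens the envelope and either opens the cylinder or pretends to, out of the study doctor's sight.

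After arrival in hospital, once the patient is intubated or intubation has been decided against, "the assistant will hand over the envelope containing the randomization as a part of the written treatment documentation". The consequence is stated openly: "The allocation will thus be revealed to the personnel taking over responsibility for the patient". The reasons given are further hospital care and assessing the need for more INO. The study doctor is left out of this disclosure, and "The study doctors are specifically instructed not to try to obtain information on allocation".

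For day 28, the follow-up paragraph of Section 3 says: "This follow up visit will be a chart- review with or without interview with treating physician at main hospital admission". Section 6.1.4 adds that the data are obtained by contacting the admitting hospital. On the day-28 CRF, Section 9.1 says: "This will be filled out by investigator if patient admitted to OUH, or by treating doctor in cooperation with investigator", the latter for patients admitted elsewhere. This form carries secondary and exploratory endpoints and safety data. Section 9.2 makes it the first source for GOS-E. Section 8.3 runs SAE collection to day 28, using discharge notes and the treating physician.

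**The concern.** The people and the record that are told the arm at handover are the people and the record that later supply the day-28 outcomes. GOS-E is the trial's only measure of functional outcome, and grading it from notes or an interview calls for judgement. So does deciding which events in a long intensive-care chart count as serious and whether INO may have caused them. Section 8.1.3 makes judged causality the test for an adverse reaction. An assessor who knows the arm can move these judgements in either direction, and the analysis could not detect or correct this afterwards. At stake are one secondary efficacy endpoint and most of the 28-day safety comparison, in a trial presented as blinded.

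**Working it through.** No figure is in dispute, so the check sets the sections side by side.

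**1. Who learns the allocation, and when.** Under 10.2 the handover is routine for patients who reach hospital. It does not depend on clinical need. The allocation goes to the receiving personnel and into the written treatment documentation.

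**2. Who supplies the day-28 data.**

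| Admitted to | Who completes the day-28 CRF (9.1) | Source (Section 3, 6.1.4, 8.3) | Exposure to the allocation |
|---|---|---|---|
| OUH | Investigator | Chart and discharge notes, with or without interview of the treating physician | Likely, not certain: the documentation includes the envelope, but nothing says that the investigator sees it |
| Another hospital | Treating doctor with the investigator | The same, plus the treating doctor's own knowledge | Expected where that doctor was on the receiving side |

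**3. Which outcomes can be moved.**

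| Outcome | How it is determined | Open to assessor bias? |
|---|---|---|
| Primary, change in SpO2 from t0 to t1 | Read at allocation and at 5 minutes (6.1.2) | No. Section 5.3 puts the intubation decision after those 5 minutes, and handover comes later still |
| Other measurements before handover | Monitor or study doctor | No |
| Mortality, laboratory values | Fact or assay | Not materially |
| GOS-E, day 28 | Graded from chart or interview | Yes |
| SAEs after handover | Seriousness and causality judged (8.1.2, 8.4) | Yes |
| 2.5.1, need for INO after EOI | Start, duration, device, dose, whether it continued the intervention | A factual item, but the answer can itself show the arm |

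**4. Which safeguards exist.** The instruction in 10.2 asks study doctors not to seek the allocation. It does not help an assessor whose task is to read the record that holds it. Section 7.3 says all investigators work in the prehospital or emergency setting, so the day-28 investigator may also be a study doctor. In that case the chart review works against 10.2's aim of keeping the allocation from study doctors. No section provides for a chart with the allocation removed or for an assessor kept from it.

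**5. Size.** The protocol plans at least 54 patients but gives no split between OUH and other hospitals. If all 54 reach a day-28 assessment, the number whose form is completed by an outside treating doctor could lie anywhere from 0 to 54. The protocol gives no GOS-E distribution and no SAE rate, so the bias cannot be estimated. The sample size of 54 rests on the 5-minute SpO2 change and is unaffected.

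**The case against.** The strongest reply is that the disclosure is deliberate, explained and made for patient care, and that little depends on it. The primary endpoint precedes it, GOS-E is one of nine secondary endpoints under the primary objective, and most of the others are readings or hard events. SAE judgement is also constrained. Section 8.2.2 lists expected events, 8.3 asks for them specifically at day 28, 8.4 applies WHO-UMC causality criteria, and 8.5 has the sponsor evaluate seriousness, causality and expectedness of the SAEs reported to it.

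Much of this stands, and it limits the point to the judgement-based outcomes. It does not remove it. Fixed criteria still have to be applied by someone. Section 8.2.2 keeps listed expected SAEs, renal failure and cardiac arrest among them, in the CRF without reporting to the sponsor, so 8.5 describes no second evaluation of those.

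Three stronger readings are tempting, and the protocol does not support them:

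- **That 10.5 contradicts 10.2.** The sentence "The treatment allocation will be revealed after the database lock and used in the statistical analysis" concerns release of the allocation for analysis. The protocol nowhere promises that hospital staff or outcome assessors stay blinded until lock.
- **That every assessor is unblinded.** Routine handover describes disclosure to the receiving team. The interview is optional, and 10.2 does not say that the envelope enters the electronic record.
- **That only the doctor who gave the treatment is told not to seek the allocation.** The instruction covers the study doctors generally, and a written blinding instruction is planned.

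Nor is this a matter for the SAP. Who assesses an outcome, and from which record, is trial conduct that 9.1 and 10.2 already fix.

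**Conclusion.** The point holds in limited form. Followed as written, the plan leaves GOS-E and the seriousness and causality of SAEs after handover open to assessor bias, in a direction and amount that the documents do not allow one to state. The fault lies in the unprotected assessment, not in telling the receiving team.

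This rests on two assumptions: that the envelope stays with the documentation used at day 28, and that treating doctors who were told the arm still know it or can find it. The first is the natural reading of 10.2 but is not spelled out for OUH. The second is expected rather than certain. The correction is worth making because it is cheap, but the primary conclusion does not depend on it.

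**What to change.** Keep the handover to the receiving team and change what follows:

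- **6.1.4 and 9.1:** state that treating doctors supply facts only (status, laboratory values, descriptions of events). GOS-E and SAE seriousness and causality are assigned by an existing study investigator who has not seen the allocation.
- **10.2:** keep the envelope out of the material given to that investigator, while leaving it available to the treating team. State who is blinded and until when, covering the study doctor, the receiving team, the day-28 investigator and the analyst.
- **Day-28 CRF:** move 2.5.1 to a separate page, completed after GOS-E and the SAE judgements. Add a box for whether the allocation was known at assessment (yes/no).

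The box makes a sensitivity analysis possible. It is filled in after randomization and may itself depend on the arm, so that analysis should be read as descriptive.

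The cost is protocol and CRF wording, one page split and one tick box, with no extra staff. It takes slightly more coordination, since investigators must ask treating doctors not to mention the arm. Some assessments will still be flagged as unblinded, for example where INO entries appear in the chart.
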